# Study Procedures

## 4.1 Study Design

This is a clinical trial with a participant-blinded, cross-over study design with repeated-measures assessments will take place at each site. Short-term, in-lab sessions will be used to address Aim 1 (i.e., comparing in-lab *emulator* trials to in-lab corresponding *actual* AFO trials) and the Exploratory Aim (comparing in-lab patient-optimized emulator trials to in-lab prescribed *actual* AFO trials). Aim 2 will compare short-term in-lab trials with longer-term follow-up using corresponding *actual* AFOs. We will assess user preference, satisfaction, perceived mobility and performance in *emulated* and *actual* AFOs to determine whether the emulator and/or a brief trial of *actual* AFOs can predict user mobility and AFO preference following longer term use in the community environment.

See section 5.5 below for data collection procedures.

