## 4.5 Study Evaluations

Prior to enrolling and consenting, participants must meet the inclusion criteria described above. Once consented, AFOs will be fit to each subject at an initial visit, based on manufacturer recommendations for foot size and body weight. Additional fitting sessions may be utilized to ensure a good fit to the individual for all three actual AFOs to be evaluated.

Participants will undergo up to three in-lab sessions: testing the emulated AFOs, testing the actual AFOs, and an optional exploratory aim session of user-selected AFO properties. Participants will undergo three 2-week periods where participants will be instructed to wear the study AFO instead of their clinically-prescribed AFO for all usual activities of daily living. After two weeks of wearing each AFO, participants will return to the laboratory for follow-up evaluation (Figure 1). Injury history and participant demographics will be collected at the initial intake session.

Participants will be block randomized to ensure similar numbers of participants are assigned to each of three AFO testing sequences and similar numbers of participants undergo either the emulated in-lab session or actual AFO in-lab session first.

**Emulated AFO testing session**. Participants will begin by walking on a treadmill in the emulator to become accustomed to its use. Participants will wear the emulator’s end effector the way they would their clinically prescribed AFO and the study orthotist will be present to make any necessary adjustments. The emulator parameters will be adjusted by the research staff member in real-time as the subject walks so they experience the range of emulated AFO conditions to be tested. After the emulator accommodation period, participants will trial three emulated AFOs in a randomized order. Participants will complete an Activities Trial and patient reported outcomes (described below).

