**Actual AFO testing session.** Prior to the start of the testing session, participants will be fit with the three actual AFOs to be worn during the data collection. Fitting will be done according to the routine standard of clinical care (e.g. test device for the custom AFOs). On the day participants complete the actual AFO testing, they will walk on the treadmill in each AFO condition to acclimate prior to testing. Then, participants will undergo the same Activities Trial as in the emulated AFO testing session (described below). The same questionnaires will be completed to identify patient-reported outcomes. In the actual AFO testing session, participants will additionally complete a series of performance tests described below.

**Two-week follow up sessions**. Participants will complete two-week long community trials in each of the three actual AFO conditions in a randomized. AFOs will have already been fit to each subject as described above. Participants will be instructed to wear the study AFO instead of their clinically-prescribed AFO for all usual activities of daily living. After two weeks of wearing each AFO, participants will return to the laboratory for follow-up evaluation; Patient-Reported Outcomes and Performance Tests will be assessed. A subset of participants may also have the activities trial collected and/or gait biomechanics collected at the two-week follow up sessions.

**The Exploratory Session** will compare a participant’s clinically prescribed AFO (clinician optimized) to a participant-optimized setting on the emulator. Stiffness will be the optimized parameter. In this exploration, participants will be allowed to dial in and change the stiffness parameters on the emulator so that they self-identify an optimal value (patient-optimized).

**Figure 1.** Study Overview

**
[figure not shown]
**

**Activities Trial**. The activities selected are intended to represent a range of activities commonly encountered in the community environment (Table 1). As detailed below, activities will be assigned in a manner specific and appropriate to the individual patient (e.g., participants of a lower mobility or with contraindications will not be asked to run). Each speed and activity condition will take place for at least 30-seconds and rest will be provided between activities as needed. After each AFO condition is complete, participants will rest for at least 10 minutes before engaging in the next AFO condition.

| **Activities Trial** |
| --- |

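### Three unlisted AFO sequences, with no stated link between stages, leave carry-over free to pass as agreement if it is large enough

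*Protocol*

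**What the plan says.** Protocol section 4.1 describes a "cross-over study design with repeated-measures assessments". Section 4.5 sets up block randomisation on two factors. Similar numbers are to be "assigned to each of three AFO testing sequences", and "similar numbers of participants undergo either the emulated in-lab session or actual AFO in-lab session first". The three sequences are not written out.

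The same section then mentions order separately by stage:
- **Emulated session:** "participants will trial three emulated AFOs in a randomized order".
- **Actual in-lab session:** no order is given.
- **Community stage:** "community trials in each of the three actual AFO conditions in a randomized", where the sentence stops in the text at hand.

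None of these statements is tied to the three sequences or to another stage.

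On spacing, "Participants will undergo three 2-week periods" and "After two weeks of wearing each AFO, participants will return to the laboratory for follow-up evaluation"; no washout between periods is described. In the lab, at least 10 minutes of rest separates one AFO condition from the next.

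Section 4.6 regresses the later-stage score on the earlier-stage score with a random participant intercept. It names no period, sequence or preceding-AFO term. The power simulation rejects when the slope differs from zero.

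**The concern.** The primary outcome is a subjective 10-point preference rating, so a contrast with the device worn just before is plausible: a stiff AFO may make the next one seem soft. If the AFO before a given AFO tends to be the same in both stages being compared, its influence moves that AFO's score the same way in predictor and outcome. A slope test against zero cannot tell this from emulator fidelity (Aim 1) or from prediction of community preference (Aim 2).

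Two features decide how far this can happen: which orders are used, and whether the order is drawn afresh at each stage. The first is fixed at three of a possible six without listing them. The second is not stated. Both are settled when the randomisation list is made, so a later analysis plan can only partly repair them.

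**Working it through.** **Inputs from the protocol.** Three AFOs, three sequences and two session orders (4.5). N = 50 evaluable and 56 in total, with a null hypothesis of slope zero (4.6). The total follows from 50 × 1.12 = 56 (dividing instead gives 50/0.88 = 56.8) and is not in dispute. The stated 97% and 98% power cannot be recomputed, because the pilot slope and residual error are not given.

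**Step 1: which sets of three are possible.** There are 3! = 6 orders and 20 sets of three. Only two sets put each AFO once in each position: ABC/BCA/CAB and ACB/BAC/CBA. The same two are the only sets in which every AFO has a single predecessor. In ABC/BCA/CAB, B follows A twice, C follows B twice and A follows C twice; each AFO is first once. The other 18 sets avoid a fixed predecessor for every AFO but unbalance position. With all six orders, each AFO follows each of the other two equally often (twice and twice).

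**Step 2: effect on AFO means.** Let AFO k shift the next rating by L_k.
- Cyclic ABC/BCA/CAB: mean shift of B is (2/3)L_A and of A is (2/3)L_C, so B − A is biased by (2/3)(L_A − L_C).
- Six orders: B is shifted by (1/3)(L_A + L_C) and A by (1/3)(L_B + L_C), so B − A is biased by (1/3)(L_A − L_B).

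This describes AFO means. The planned test is of a slope, hence step 3.

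**Step 3: effect on the slope test.** Simulation with N = 50, three AFOs, no true relation between stages, and predecessor shifts of −c, 0 and +c within-person SD acting alike in both stages. The test is the within-participant slope at two-sided 0.05, standing in for the random-intercept model; there were 8,000 datasets per cell. The values of c and the 0.05 level are assumptions. False-positive rates:

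| Scheme | c = 0 | c = 0.25 | c = 0.5 | c = 1.0 |
| --- | --- | --- | --- | --- |
| Three cyclic orders, reused | 5% | 6% | 22% | 97% |
| Three cyclic orders, redrawn | 5% | 6% | 17% | 83% |
| Six orders, reused | 5% | 6% | 23% | 97% |
| Six orders, redrawn | 5% | 5% | 6% | 11% |

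Runs at N = 48 gave 21-22%, 15-16%, 20-23% and 6-7% for the four schemes at 0.5 SD, and 5-7% throughout at 0.25 SD.

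**Step 4: can later adjustment repair it?** With N = 48, the variance of an AFO contrast adjusted for participant and period is 2/48 = 0.042 σ². Adding the preceding AFO raises it to 0.208 σ² with three cyclic orders (0.208/0.042, about 5-fold) and to 0.052 σ² with six (0.052/0.042, about 1.25-fold). Order terms are therefore a costly remedy under three cyclic orders and a cheap one under six.

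**The case against.** A reader might infer that only three of the six orders are ever used, that each AFO always follows the same other AFO, and that one sequence governs all three stages. The protocol supports none of these as fact. It does not list the sequences or say they are cyclic, and in 18 of the 20 possible sets the fixed-predecessor claim fails. Even in a cyclic set it does not apply to the AFO tested first. The separate mentions of randomised order for the emulated and community stages are at least as consistent with separate draws, and the figure showing the study overview is not available here.

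It is also tempting to blame the number of orders alone. The table does not bear that out: six orders reused inflate the error as much as three.

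Carry-over may also be small. Participants experience the range of emulated settings before rating any, and acclimate on the treadmill in each actual AFO. They rest between conditions, and community outcomes come after two weeks of wear. Carry-over in a short laboratory trial need not resemble carry-over across community periods, and the mechanism needs it to act alike in both stages. Finally, period and preceding-AFO terms commonly belong in an analysis plan, which is not at hand.

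These points limit the claim and make its size uncertain. What stands is that any three orders force a choice between a fixed predecessor and unbalanced position. Nor does the protocol exclude the schemes in which carry-over inflates the test.

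**Conclusion.** The concern holds in conditional form. Section 4.5 fixes three sequences without listing them and leaves open whether order carries over between stages. If the sequences are position-balanced, predecessor is largely tied to AFO even when order is redrawn.

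Whether this matters depends on a quantity the protocol does not give. At 0.25 within-person SD it can be ignored. At 0.5 SD, false positives reach about 15-23% under every scheme examined except six orders redrawn at each stage, which stays at about 6%. These figures assume carry-over that is specific to the preceding AFO and similar in both stages, no true relation between stages, and a cyclic set where three orders are used. The absence of a term for order in section 4.6 is not counted as a fault in itself. The point is worth acting on because the remedy is cheap and protects the main inference of Aims 1 and 2. The sample size of 56 is unaffected.

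**What to change.** In section 4.5, replace the three sequences by all six orders in balanced blocks. Draw a participant's order independently for the emulated session, the actual in-lab session and the community trials. Apply this to participants not yet randomised. Make the block-randomisation paragraph and the stage descriptions agree with it, including the incomplete sentence on the community trials and the actual in-lab session, for which no order is given. Record the order used at each stage so that period and preceding AFO can enter a sensitivity analysis.

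Both parts are needed: six orders without redrawing do not help, and redrawing from three cyclic orders helps only a little.

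The cost is a new randomisation list, with no added visits or participants. Six orders by two session orders make 12 cells, so 56/12 = 4.7, or 4-5 participants per cell, in place of 56/6 = 9.3. If enrolment has begun, the list changes partway and the two schemes should be identifiable in the data.

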***Potential Benefits to Participants***

There are no direct benefits to participants for taking part in the study. However, others may benefit in the future from the information learned during this study. The possible benefits to others are creating a better process for determining which AFO is best to prescribe to a patient. Participants will be compensated for their time.

## 4.6 Data Analysis

**Aim 1.** The purpose of Aim 1 is to test the ability of the AFO emulator to reproduce the user experience of wearing actual AFOs during different activities (walking, running, stair climbing; level ground, ramps) in individuals with lower limb musculoskeletal injury. We will consider the outcome measures as continuous response variables in the statistical analysis. We will evaluate the data from the in-lab actual and in-lab *emulated* sessions using a linear mixed effect (LME) regression with the *emulated* AFO data as the independent fixed effect, the *actual* AFO data as the dependent fixed effect, and subject participant as a random intercept.

**Hypothesis 1A**. In Specific Aim 1A, we are testing the hypothesis that the experimental AFO preference measured during the in-lab *emulated* session will be significantly correlated with the experimental AFO preference measured during the in-lab *actual* session. This model estimates a change in *actual* AFO preference per unit change of *emulated* AFO preference.

**Hypothesis 1B**. In Specific Aim 1B, we are testing the hypothesis that self-reported measures and biomechanics will be significantly correlated between the in-lab *emulated* session and the in-lab *actual* session. This model operates the same as in 1A, substituting measures of function and mobility for preference.

**Aim 2.** The goal of Aim 2 is to determine if the in-lab (*emulated* and *actual*) measurements are a good predictor of the longer-term measurements made following a take home trial. To perform this analysis, we compute a similar LME regression as Aim 1 with the *emulated* *or actual* in-lab AFO data as the independent fixed effect, the *actual* take-home trial AFO data as the dependent fixed effect and subject participant as a random intercept.

**Hypothesis 2A**. In Specific Aim 2A, we are testing the hypothesis that the experimental AFO preference measured during the in-lab *emulated* session will be significantly correlated with the experimental AFO preference measured during the take home-trials. This model operates the same as in 1A, substituting measures of take-home trial preference as the dependent variable.

**Hypothesis 2B**. In Specific Aim 2B, we are testing the hypothesis that the experimental AFO preference measured during the in-lab *actual* AFO session will be significantly correlated with the experimental AFO preference measured during the take home-trials. This model operates the same as in 1A, substituting measures of take-home trial preference as the dependent variable.

**Hypothesis 2C**. In Specific Aim 2C, we are testing the hypothesis that measures of preference will be significantly correlated between the *emulated* in-lab session and measures of performance and self-reported measures of mobility at the take-home trials. This model operates the same as in 2A, substituting measures of performance and self-reported outcomes for preference as the dependent variable.

**Hypothesis 2D**. In Specific Aim 2D, we are testing the hypothesis that measures of preference will be significantly correlated between the *actual* in-lab session and measures of performance and self-reported measures of mobility at the take-home trials. This model operates the same as in 2A, substituting measures of performance and self-reported outcomes for preference as the dependent variable.

**Power Analysis for Aims 1 & 2**. Our power analysis is based upon pilot data collected for a similar study using prosthetic feet which tested mobility and preference for three participants and two feet between *emulated* and *actual* sessions. Based upon the estimates of slope and residual error from the pilot data, 10,000 datasets were created for a sample size of N=50. Power, estimated as the proportion of datasets that rejected the null hypothesis of a slope equal to zero, was 97% for the preference scores and 98% for the mobility scores. To account for a 12% dropout rate (note that prior prosthetic emulator study experienced a 7% dropout rate) a total sample of N=56 participants will be tested.

**Exploratory Aim**. In this exploration, participants will be allowed to dynamically “dial-in” and change in the stiffness settings of the emulator device so that they design an optimal device to meet their needs. The *emulated* device will then be compared to the device that was clinically prescribed for them as part of usual care. To test the hypothesis a simple paired t-test will be used which compares the preference means and other outcomes measures of the patient-optimized and clinician-optimized conditions.

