## 4.2 Recruitment Methods

The study will recruit up to 56 participants with lower limb musculoskeletal trauma who are currently using an AFO. Men and women will both be recruited to the extent they are represented in the patient population. No exclusions will be made on the basis of race, ethnicity, sex, or gender.

Human subjects will be recruited from a convenience sample of eligible participants at the sites. The sites were specifically selected based on their potential for high enrollment and because they prescribe a wide range of AFO devices to patients of various mobility/activity levels and injury etiologies.

The following methods and resources may be used to recruit subjects:

1. Recruitment using medical record data is often believed to be the most effective means of achieving enrollment goals [21]. Designated research staff at the sites will screen relevant clinic lists in computerized patient record systems to identify potential participants. After review of relevant clinic lists, designated staff will go to the clinic or contact providers to ask if a patient might be a good fit for the study. If the clinician agrees that a patient may be an appropriate study participant, during an appointment the clinician will ask the patient if she/he is interested in speaking with designated study staff; patients will be given a chance to opt out. For patients who are interested, designated study staff will speak to potential participants.

2. **Clinician Referral:** The study teams at each site have built relationships with local clinic staff and have established effective clinical referral systems. Research staff will inform providers working in relevant clinics about the study and inclusion/exclusion criteria so they can refer potential participants to contact the study team. Flyers and business cards may be provided to clinicians to give to patients that are interested in the study. If a clinician informs patients about the study and the patient agrees to be contacted about it, the clinician may provide the research team with the patient’s name and they may also provide contact information. Clinicians may also provide (via in-person/on the phone) the names of patients that they are aware of who may be a good fit for the study and a study staff member will send an approach letter, make direct contact during a clinic visit, or the clinician provider may inform potential participants.

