# Privacy and Confidentiality

As with any study, it is possible, although unlikely given the impersonal nature of the data collected, that participants may experience a loss or invasion of privacy or confidentiality because of participation in this study. The risk of harm is minimal and the protections described here will be followed.

Participant data will be collected the study sites and will be entered into independent and secure databases. In general, electronic data will be coded with links stored separately, stored on password protected drives, servers will be backed up regularly, firewalls in place, and access permitted only by study team members listed on the approved IRB protocol. Hard copies of data forms will contain only codes and be stored in locked cabinets (dedicated to this study’s records), and locked offices with access only given to study team members. Informed consent documents will be stored separately along with other identifiable information (such as records necessary to have in paper form, which will be limited). Because this is a multi-site study, extra care will be taken not to share PHI or other identifiable information about participants across centers.

To protect privacy and confidentiality during data collections, all data collected will have PHI removed and participants will be issued an alpha-numeric code which will be used to track their records. Subject records will be coded with a unique identifier. The first five characters will be an abbreviation of the study (AFO Test Drive - AFOTD) to identify to which study the subject belongs followed by a site identifier (WR = Walter Reed, VA = VAPSHCS) and sequential numbering based on the subject order of enrollment. The device tested will be indicated as device 1, 2, or 3.

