# Communication Plan

All human subjects data collected as part of this study will be handled in a manner compliant with the intent and letter of the regulatory processes at each of the site. Data will be collected locally at each of the sites and initial analysis will take place at each site. No PHI or PII will be shared. Only coded data will be shared across sites. The investigators agree to adhere to any and all local policy guidelines for data sharing.

1. **Information Security and Data Storage/Movement**

Non-sensitive electronic data labeled with the study assigned codes and all 18 HIPAA identifiers removed (coded data), may be stored on password protected equipment (computers/laptops/hard drives) but will not be encrypted.

To minimize the risk of the loss of confidentiality and provide for data security, conservative data management procedures have been established at all study locations involved in this project. To facilitate successful completion of the Specific Aims, identifiable data will be shared only internally. Chart reviews of coded data will be completed locally and only coded human subjects data will be shared among the sites via file transfer software, email, and/or other electronic media (CD/DVD/USB drive). Throughout the course of the study, we may place a copy of all coded data in publicly accessible online data repositories. Additionally, we intend to make our datasets publicly available at the conclusion of the study in publications and presentations. We will also share our mechanical testing (non-human subjects) results with Humotech, the emulator vendor so they can program the system. Therefore, there are no anticipated concerns with Humotech (or others) incorporating this data as part of repository. To protect privacy and prevent breaches of confidentiality, all study procedures starting with recruitment and extending through to findings dissemination will adhere to all site and IRB policies and applicable regulations. All study staff realize the importance of keeping private personal information secure and are trained biennially at the sites to minimize this risk. All study personnel will demonstrate knowledge of these regulations by completing courses of instruction through the CITI program and local HIPAA compliance offices.

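### The Aim 1 and Aim 2 models pool two sites without a site term, so a same-direction site difference would partly enter the slope; the size depends on a difference the protocol does not give

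*Protocol*

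**What the plan says.** Protocol section 4.6 (Data Analysis) describes the Aim 1 model as a linear mixed effect regression. The emulated "AFO data as the independent fixed effect", the actual-AFO score is the response, and the only other term is "subject participant as a random intercept". Aim 2 uses a similar model with the emulated or actual in-lab score as predictor and the take-home score as response. Hypotheses 1B and 2A to 2D are each said to operate in the same way with variables substituted. In the power paragraph of section 4.6 the test is described as the proportion of datasets that "rejected the null hypothesis of a slope equal to zero".

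The trial runs at two sites. Section 4.1 describes a "cross-over study design with repeated-measures assessments will take place at each site". The Privacy and Confidentiality section puts a "site identifier (WR = Walter Reed, VA = VAPSHCS" into every participant code. The Communication Plan says "Data will be collected locally at each of the sites and initial analysis will take place at each site", but not how the sites are then combined. Section 4.6 mentions neither a site term nor centring of the in-lab score.

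**The concern.** The predictor is the raw score, so its slope blends two associations. One is within a participant: does the AFO rated higher on the emulator also get the higher rating later? The other is between participants: do people who score high in one session score high in the next? The aims concern the first, namely whether a trial on the emulator tells you how that person will find the corresponding device.

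Site is constant within a participant, so any site effect sits wholly in the second part. If fitting, instructions, laboratory set-up or case mix lift both scores at one site, the expected slope is positive even when device-level agreement is zero. Rejecting slope = 0 is the evidence offered for Hypotheses 1A to 2D, so a rejection driven by site would be read as emulator fidelity or predictive ability.

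**Working it through.** **The plan's own figures.** The total of 56 follows from 50 × 1.12 = 56 (dividing instead, 50/0.88 = 56.8, gives 57). The 97% and 98% power cannot be reproduced, because the pilot slope and residual error are not stated. Neither figure bears on site.

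**Inputs.** From the protocol: N = 50 evaluable, m = 3 AFOs, a 10-point preference scale, a random-intercept regression on the raw score, and a test of slope = 0. Assumed, because the protocol does not give them: two-sided 5% level; a 25/25 site split; participant SD σp and residual SD σe of 1/1.5, 1.5/1.5 and 1/2 points; a shift of d points between sites in both scores, same direction; true within-participant slope zero.

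**Expected slope.** With site variance s = d²/4 (equal split), the random-intercept estimator weights between-participant information by θ = σe²/(σe² + m(σp² + s)):

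- Within-participant sums: cross-product 0; squares N(m − 1)σe².
- Between-participant sums: cross-product Nm·s; squares Nm(σp² + s + σe²/m).
- Slope = θ·Nm·s / [N(m − 1)σe² + θ·Nm(σp² + s + σe²/m)], which simplifies to s / [m(σp² + s) + σe²].
- Its standard error is about 1/√(Nm) = 1/√150 = 0.082.

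For σp = 1 and σe = 1.5:

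- d = 1: 0.25/(3 × 1.25 + 2.25) = 0.25/6 = 0.042, about 0.5 standard errors.
- d = 2: 1/(3 × 2 + 2.25) = 1/8.25 = 0.121, about 1.5 standard errors.

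**Simulation of the model as written** (REML, 800 datasets per cell, participant levels uncorrelated between sessions). Each cell shows mean slope and rejection rate without a site term:

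| Shift d | σp/σe = 1/1.5 | 1.5/1.5 | 1/2 |
| --- | --- | --- | --- |
| 0.5 | 0.010, 5.8% | 0.010, 5.9% | 0.009, 5.1% |
| 1 | 0.042, 6.8% | 0.022, 6.4% | 0.036, 8.4% |
| 1.5 | 0.078, 15.8% | 0.058, 12.4% | 0.065, 14.4% |
| 2 | 0.133, 38.4% | 0.088, 19.9% | 0.103, 26.9% |

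The simulated slopes agree with the formula. Repeat runs gave 5-9% at 1 point, 9-18% at 1.5 and 17-40% at 2. With a 40/10 split and SDs 1.5/1.5, rejection was 6% at 1 point and 12% at 2. With a site term the mean slope was about 0 and rejection about 4-8% throughout. Simulation error near 5% is √(0.05 × 0.95/800) = 0.8 percentage points.

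**What a site term does not remove.** Let a participant's own level correlate 0.5 between sessions, with d = 0. The numerator of the slope becomes 0.5σp². For SDs 1/1.5 this gives 0.5/(3 + 2.25) = 0.095 (simulated 0.100). Rejection across the three SD settings was 16-38% without a site term and 16-37% with one. Adding a 1-point site shift gave 23-48% without and 14-37% with. The slope on within-participant deviations stayed at about 4-7% in every setting.

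**The case against.** **A site covariate is commonly left to the SAP, which is not at hand.** This has weight: the sentence in section 4.6 does not call its terms exhaustive, and an SAP may add site. But section 4.6 writes out the fixed effect and the random effect and carries that structure through all the hypotheses. The point changes a stated model; it does not ask for missing detail.

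**No site difference is shown.** This stands. Section 4.2 says the sites were chosen "because they prescribe a wide range of AFO devices to patients of various mobility/activity levels and injury etiologies". That describes variety among the patients seen, and a reader should not take it as evidence that the two sites differ from each other. A shift of 1.5-2 points is large on a 10-point scale.

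**Not every site difference inflates the slope.** This also stands. The random intercept down-weights between-participant information, so only part of a shift enters. Opposite-direction shifts push the slope negative, and a shift in one score alone does not bias it. For Hypotheses 2C and 2D predictor and response are different measures, so the simulated common shift does not carry over directly; a site effect on both is still needed.

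**If the patients differ by site, the association is real.** As a between-patient association, yes. It still says nothing about whether a person's ratings of different AFOs agree between sessions, which is what device selection needs.

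**A site term leaves the larger problem in place.** This is correct, and it is why the fix goes beyond site.

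**Conclusion.** The point holds as a conditional and minor weakness of the written model. Two sites are pooled on a raw score with no site term, so a same-direction site difference would partly enter the slope and favour rejection without device-level agreement. The inflation is close to nil up to about 1 point on the preference scale and about 9-40% rejection at 1.5-2 points. This rests on the assumed SDs, the 25/25 split, a two-sided 5% level and uncorrelated participant levels; a more uneven split makes it smaller.

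A reader might infer three stronger things that the documents do not support:

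- That any site difference counts as prediction. Direction and size both matter, and the leak is partial.
- That a site difference is present. No figure in the protocol shows one.
- That block randomisation within site would cure this. Section 4.5 describes balancing AFO sequence and session order. That does not alter a site's overall score level, and no calculation links it to the slope.

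**What to change.** In section 4.6, add site as a fixed effect in each Aim 1 and Aim 2 model. It is already recorded in the participant code and costs one degree of freedom and one sentence.

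In the same models, replace the raw in-lab score by two terms: the participant's mean over the AFOs, and the deviation of each AFO's score from that mean. State that the hypothesis test is on the within-participant slope. This removes both site and participant leakage and needs no extra data. The price is one further coefficient and a test that no longer draws on between-participant information, so the power statement should be rerun for the within-participant slope. No change to the randomisation is needed on this account.
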